### Component 4: an instrumental variable analysis of NHS and independent sector inpatient mental health rehabilitation services using routinely collected healthcare records

In instrumental variable analysis (IVA), patients are not directly compared with respect to the treatments received. Rather, the approach compares groups who differ in their probability of receiving the treatments (in this case, receiving inpatient rehabilitation in the NHS or the independent sector). IVA is attractive since even in the presence of unmeasured confounding it may consistently estimate the average causal effect of an exposure on an outcome. It thus mimics the conditions of a randomised trial [38]. We plan to use the extent to which each CCG ‘outsources’ inpatient rehabilitation to the independent sector as an instrumental variable (IV), because it predicts receipt of inpatient rehabilitation in the NHS or independent sector (our main exposure) but has no direct effect on successful rehabilitation (our outcome). In other words, it is associated with successful rehabilitation only through its effect on the type of service received and has no indirect effect on the outcome via any other pathway. It thus meets the conditions required for an IV. The IV here is the proportion of inpatient rehabilitation beds each CCG commissions from the independent sector per 100,000 CCG population. The CQC have shared relevant data with us that will allow us to generate this variable for each CCG in England.

We will request NHS England to develop a dataset of all individuals in a mental health inpatient rehabilitation unit (NHS or independent sector) on 1st February 2021, the ‘census date’. This dataset will include all inpatient service use over the following 18 months (i.e. up until 1st August 2022) which will show whether the person has been discharged from the rehabilitation unit during this period or not, the date of discharge, and the admission and discharge dates of any subsequent inpatient admissions. The dataset will be comprised of the following variables:

Anonymous patient identifier (linked to NHS number with key held by NHSE and not available to the research team).The CCG funding the inpatient rehabilitation admission.Baseline (i.e. census date: 1st February 2021) rehabilitation admission provider: NHS/Independent.Start date of the baseline rehabilitation admission.Start date of the baseline rehabilitation admission ‘spell’ (most inpatient rehabilitation patients are transferred from another inpatient ward; the ‘spell’ refers to the period when the patient was first admitted from the community to the point they are discharged to the community, including any transfers between inpatient wards).Gender at baseline.Age at baseline.Ethnicity.Rating of each Health of National Outcome Scale (HoNOS) item (12 in total) for HoNOS assessments recorded between the date 12 months before the census date (i.e. 1st February 2020) and the 18-month end date (i.e. 1st August 2022).HoNOS assessment dates.Inpatient service use during the cohort period (i.e. baseline date to 18-month end date).Discharged from the baseline inpatient rehabilitation admission: Yes/No.Date of discharge from the baseline rehabilitation service.Start and end date of any inpatient admission following discharge from the baseline rehabilitation admission, and the 18-month end date.

The 1st February 2021 was set as the census date in order that the 18 month study period (a) minimised the amount of time when Trusts were still affected by the COVID-19 pandemic and (b) avoided the impact of the cyber-attack of mid-August 2022 which affected several NHS Trusts. Trusts affected by the cyber-attack were unable to provide any data, including inpatient service use data, to NHS England for several months following the attack.

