## Background

Most people diagnosed with a severe mental illness such as schizophrenia recover at least partially, but around 25% develop longer term, complex problems that require mental health rehabilitation services [1, 2]. These include persistent, severe ‘positive’ symptoms (delusions and hallucinations) and ‘negative’ symptoms (reduced motivation, verbal communication and emotional reactivity), alongside poor organisational skills due to specific cognitive impairments associated with the illness. Recovery is often further complicated by substance misuse and co-morbid physical health problems (such as obesity, diabetes, cardiovascular and pulmonary disease). Some people also have pre-existing conditions such as intellectual impairment and/or developmental disorders, including those on the autism spectrum. These multiple problems impact negatively on the person’s social and everyday functioning (self-care, housework, shopping, cooking, budgeting and interpersonal skills) and may lead to challenging behaviours [3]. Many will struggle to engage in community activities or gain employment, and over half are vulnerable to self-neglect and exploitation [4, 5]. In short, without appropriate treatment and support, quality of life for people with complex psychosis is poor.

Due to their complexity, admissions to inpatient rehabilitation services are longer than general (‘acute’) mental health admissions and community support costs for this group are high; it has been estimated that around half the total health and social care budget for mental health is spent on people with complex psychosis [6]. Nevertheless, our previous research has shown that with access to local NHS rehabilitation services, most people can gain the skills to manage with less support over time, graduating from inpatient care to higher, and then lower, supported accommodation [7, 8]. However, recent years have seen major disinvestment in NHS inpatient mental health rehabilitation services across England and increasing reliance on the independent sector.

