In 2018, the Care Quality Commission (CQC) surveyed all providers of inpatient mental health rehabilitation services in England [9]. They reported the cost of inpatient rehabilitation to be over £500 m per year, with the independent sector providing around half the 4,400 beds in the country. They noted that use of the independent sector varied greatly by Clinical Commissioning Group (CCG) and admissions to independent sector rehabilitation units were twice as long as those at NHS units. Although the cost per day was similar, admissions to the independent sector therefore cost twice as much. The CQC also found that patients treated in the independent sector were much further from home than those receiving NHS care and they raised concerns about the social dislocation this caused for patients. They highlighted a lack of evidence-based rehabilitation being provided in many units and questioned whether the current system represented an appropriate use of public funds, stating ‘Too often, these…rehabilitation hospitals are in fact long stay wards that institutionalise patients, rather than a step on the road back to a more independent life in the person’s home community.’

The CQC report [9] attracted considerable negative press [10, 11] and prompted a national initiative by NHS England (‘Getting It Right First Time’– GIRFT) to encourage Clinical Commissioning Groups (CCGs) to invest in local NHS mental health rehabilitation services [12]. The recently published NICE Guideline on mental health rehabilitation modelled the potential cost savings if all inpatient rehabilitation were to be provided by the NHS and estimated this at £52,000 per patient (an estimated total saving of over £100 m per year) [13]. However, this may be overly optimistic since there have been no studies comparing the quality and outcomes of NHS and independent sector providers of rehabilitation. A reversal of the current system risks wasting the expertise gained by the independent sector and major investment may be required to rebuild NHS services. Furthermore, there may be bias in the CQC data since NHS Trusts may be transferring patients with higher complex needs to the independent sector, necessitating longer admissions [14, 15].

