#### Interview content

Topic guides have been developed by the Project Management Group and reviewed and revised through consultation with our patient and public involvement (PPI) and Expert Reference Group members. Separate topic guides have been developed for inpatient rehabilitation service staff patients, relatives/carers, community staff, and senior managers and commissioners.

Topic guides for staff cover multilevel factors, key factors, and processes that illuminate relationships between context and outcomes. Thus, interviews with senior managers and commissioners will explore the ‘external system’ (economic, political, and professional milieu) [31] and decision-making processes related to transfers to the independent sector compared with those who remain in the NHS (e.g. capacity, funding, patient characteristics) and how these are negotiated. Focus groups and interviews with unit staff will explore contextual, ‘internal’ factors (culture, ethos, attitudes, resources, prioritisation and intensity resource allocation: staffing levels, recruitment, skill mix, training; structure and organisation). Transfers to the independent sector are criticised for the social dislocation of patients and the failure to maintain connections to NHS services, family and neighbourhood. We will specifically explore this issue, considering NHS and independent sector perspectives. Our in-depth interviews with patients will cover: satisfaction with the unit’s facilities; the content of the rehabilitation programme provided; staff attitudes (e.g. communication, helpfulness, service user empowerment); barriers to accessing community resources; maintaining contact with family/friends; joint decision making and discharge planning. Interviews with family/informal carers will explore satisfaction with services and any barriers to their involvement. Interviews with community staff will explore their perspectives on the patient’s current care in the inpatient rehabilitation unit and any barriers to their involvement. We do not anticipate any of the interviews or focus groups to include topics that might be sensitive or upsetting, nor do we expect the disclosure of criminal or other activities which require action.

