#### Analysis

Using appropriate regression models, we will estimate associations (1) between the IV and type of service received (NHS or independent sector) and (2) between the IV and successful rehabilitation. We will then investigate imbalance in key confounding factors (e.g. age, gender, latest HoNOS score) for the IV. The main analysis is a regression model using only the IV value as the predictor of outcome (total bed days over the 18 months follow-up). Then as part of the sensitivity analysis we shall rerun the regression analysis including key confounding variables that are potentially unbalanced in the regression model, in addition to the IV. As part of sensitivity analyses, different thresholds will be explored to construct the IV, based on the probability of CCGs outsourcing inpatient rehabilitation to the independent sector. Bias due to missing data will be investigated if applicable and sensitivity analyses under plausible missing data assumptions performed. Multiple imputation for missing data will be used if appropriate.

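### Component 4 states the instrument's validity as fact, and the checks it names are all at patient level although the instrument varies only between CCGs

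*Protocol article*

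**What the plan says.** The Component 4 introduction defines the instrument at CCG level: "The IV here is the proportion of inpatient rehabilitation beds each CCG commissions from the independent sector per 100,000 CCG population". It says that outsourcing predicts the sector in which a patient is treated, and that it "has no indirect effect on the outcome via any other pathway. It thus meets the conditions required for an IV". No caveat or test is attached, and the same paragraph likens instrumental variable analysis to a randomised trial.

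Component 4, Analysis, makes the main analysis a regression of total bed days on the instrument with no other predictor. It plans to look for "imbalance in key confounding factors (e.g. age, gender, latest HoNOS score) for the IV". Two sensitivity analyses follow: one adds confounders that may be unbalanced, the other varies the threshold used to build the instrument. The variable list for the NHS England extract includes the funding CCG but no characteristic of that CCG.

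Elsewhere, Component 2 (Interview content) plans to explore how transfers to the independent sector are decided, giving as examples "e.g. capacity, funding, patient characteristics". The Background says that "recent years have seen major disinvestment in NHS inpatient mental health rehabilitation services across England and increasing reliance on the independent sector", and reports that use of the sector differed widely between CCGs.

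**The concern.** An instrument at CCG level is threatened by whatever differs between CCGs. If areas that outsource heavily also have less local provision for patients to move on to, their patients may stay longer in either sector. Outsourcing would then be associated with bed-days by a route that does not pass through sector. This breaks independence if local shortage drives both, and exclusion if outsourcing itself reduces local provision.

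The plan treats this route as ruled out in Component 4, while Component 2 is still to investigate why CCGs transfer patients. Age, gender and HoNOS scores do not measure local provision, so balance on them would say little about it. At stake is the causal reading of Component 4, the part of the programme meant to deal with unmeasured confounding.

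**Working it through.** **1. The plan's own figures (Component 3, Sample size estimation; Component 4, Sample size).** A two-sample t test at 0.38 SD, 90% power and two-sided 5% needs 147 per group, 294 in all. The variance inflation factor is 1/(1 − 0.16) = 1.19, and 294 × 1.19 = 350. The design effect is 1 + (14 − 1) × 0.06 = 1.78, and 350 × 1.78 = 623. Expected data are 4,400 × 0.85 = 3,740, which is 6.0 times 623. All of these reproduce, and none is disputed.

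**2. What a direct CCG path does.** Compare high- and low-outsourcing CCGs. Let β be the true sector effect in days, p the difference in the probability of independent sector placement, and g the difference in bed-days that does not run through sector.

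- Regression on the instrument alone, as the main analysis is worded: contrast = βp + g.
- Ratio (instrumental variable) estimate: β + g/p.

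Either way, a direct effect g has the same weight as a sector effect of g/p. The documents give neither g nor p, so the values below are assumptions. With β = 0:

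| g (days) | p = 0.3 | p = 0.5 | p = 0.7 | p = 0.9 |
|---|---|---|---|---|
| 5 | 16.7 | 10.0 | 7.1 | 5.6 |
| 10 | 33.3 | 20.0 | 14.3 | 11.1 |
| 20 | 66.7 | 40.0 | 28.6 | 22.2 |

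A spurious difference equal to the plan's 42-day target would need g = 42p, that is 12.6, 21.0, 29.4 or 37.8 days at the same four values of p.

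**3. Sample size gives no protection.** g/p does not contain N. Take SD 113, design effect 1.78 and an equal split of CCGs into high and low. The effective sample is 3,740/1.78 = 2,101, and the standard error of the contrast is 2 × 113/√2,101 = 4.9 days. With no sector effect, a direct effect of 5, 10, 15 or 20 days would be declared significant 17%, 53%, 86% or 98% of the time. At the required 623 patients the effective sample is 350 and the standard error 12.1 days, and the 10-day case would be declared significant 13% of the time. More data make the false finding more likely.

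**4. Simulation.** Settings: 267 CCGs of 14 patients (3,740/14 = 267; the number of CCGs is assumed), intracluster correlation 0.06, no sector effect, a two-stage estimator adjusted for one patient covariate, 300 runs per setting. *Shortage* is a CCG-level variable related to outsourcing.

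| Correlation of shortage with outsourcing | Days per SD of shortage | Patient covariate only: mean estimate, rejections | CCG shortage added |
|---|---|---|---|
| 0 | 10 | −1.0 days, 8% | −1.0 days, 7% |
| 0.3 | 10 | +10.3 days, 21% | −0.8 days, 4% |
| 0.6 | 10 | +21.8 days, 67% | −0.3 days, 6% |

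Patient-level adjustment leaves the bias in place. Adjustment for the CCG-level variable removes it. With zero correlation there is no material bias to remove.

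**The case against.** The strongest reply is that the documents do not show a bypass route.

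- A reader might infer that the protocol contradicts itself by saying that capacity and funding drive both outsourcing and discharge. It does not say this. The Component 2 text is an interview topic guide about transfers, and the disinvestment sentence describes a national trend. The statement that "with access to local NHS rehabilitation services, most people can gain the skills to manage with less support over time" concerns NHS rehabilitation itself, so it can equally describe the sector effect being estimated. No sentence says that high-outsourcing CCGs have less provision for discharge.
- A reader might also infer that a small local effect is bound to be magnified, or that the bias must run against the independent sector. Neither follows. Magnification depends on p, which is not given, and the main analysis is worded as a regression on the instrument, not a ratio. The direction depends on a relationship that nobody has measured.
- Some handling is present. The balance list is introduced as examples, unbalanced confounders enter a sensitivity analysis, and a fuller covariate list may sit in an analysis plan that is not shown. Because the instrument is built from CQC data outside the extract, CCG-level linkage has to happen anyway.
- Forcing CCG covariates into the main model would be debatable. Total rehabilitation beds, for instance, do not measure supported accommodation, and may overlap with an instrument scaled per 100,000 population.

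All of this stands and limits the point. It does not answer two things: validity is declared as established, and none of the checks named is at the level at which the instrument varies.

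**Conclusion.** The point holds as a matter of wording and of missing safeguards, not as a demonstrated bias. Component 4 presents two untestable conditions as met, and the protocol's background gives reason to doubt them. With the main model and named checks as written, a CCG-level path to bed-days could be reported as a sector effect. Bias requires a CCG factor related both to outsourcing and to bed-days by a route other than sector, and the documents quantify neither link. Every figure for its size is therefore illustrative: a 10-day direct effect corresponds to 11 to 33 days of apparent sector effect for p from 0.9 down to 0.3, and to nothing if the link is absent. What does not depend on those assumptions is that the large sample would not reduce the bias.

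**What to change.** **Component 4, introduction.** State that exclusion and independence are assumptions, give the reasons for thinking them plausible, and make the comparison with a randomised trial conditional on them.

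**Component 4, Analysis.** Keep the main model and add:

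1. An instrument balance table on CCG-level characteristics, linked through the funding-CCG field: for example deprivation, rurality and, where available, local rehabilitation or supported accommodation provision.
2. A sensitivity analysis adjusting for those characteristics.
3. A sensitivity analysis showing how the Component 4 estimate changes over a range of direct CCG effects, with the range stated before the data are seen.

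**Cost.** A data merge, one extra table and somewhat wider intervals in the adjusted sensitivity analysis. Characteristics that overlap closely with the instrument will weaken it, so the choice needs a stated rationale.

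### The Component 4 instrument is defined as a proportion per 100,000 population, which is not a coherent quantity and is not the outsourcing measure for which the plan argues validity

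*Protocol article*

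**What the plan says.** Component 4 of the protocol article describes its instrument in three ways.

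- As a concept, in the opening text of Component 4: "We plan to use the extent to which each CCG ‘outsources’ inpatient rehabilitation to the independent sector as an instrumental variable (IV"). The Component 4 sample size section uses the same concept and expects it to predict sector strongly.
- As an operational definition, later in that opening text: "The IV here is the proportion of inpatient rehabilitation beds each CCG commissions from the independent sector per 100,000 CCG population".
- As a basis for sensitivity analyses, in the Component 4 analysis section: "different thresholds will be explored to construct the IV, based on the probability of CCGs outsourcing inpatient rehabilitation to the independent sector".

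The validity argument comes before the operational definition and concerns the concept. The article says that "it is associated with successful rehabilitation only through its effect on the type of service received" and that it "has no indirect effect on the outcome via any other pathway", and concludes: "It thus meets the conditions required for an IV".

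On the model, the Component 4 analysis section states: "The main analysis is a regression model using only the IV value as the predictor of outcome", the outcome being total bed days over 18 months. Balance over the instrument is to be checked for "key confounding factors (e.g. age, gender, latest HoNOS score) for the IV", and unbalanced factors enter a sensitivity analysis. The factors named are patient-level examples. CCG population and total bed supply are not mentioned.

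**The concern.** A proportion is already free of scale, so attaching a population denominator leaves two literal readings. One is the outsourced share divided by CCG population. The other is a count rate: independent-sector beds per 100,000 people. Neither ranks CCGs by how likely their patients are to be placed in the independent sector, which is what the concept and the sensitivity wording both describe.

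The instrument is the central variable of Component 4, and the main model contains nothing else. Two things are at stake.

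- **Strength.** The sample size section rests the adequacy of the IV analysis on a strong instrument. A variable that mixes the share with population or bed supply predicts sector less well than the share itself.
- **Validity.** The article gives reasons why outsourcing should affect bed days only through sector. It gives none for CCG size or bed supply per head, and either could plausibly be related to bed days by another route.

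**Working it through.** **The plan's own figures.** The Component 4 sample size reproduces:

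- 294 × 1.19 = 349.9, rounded to 350
- design effect 1 + (14 − 1) × 0.06 = 1.78
- 350 × 1.78 = 623
- 4,400 × 0.85 = 3,740
- 3,740 / 623 = 6.0

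None of these uses the scale of the instrument, so none changes.

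**Target quantity.** The cohort is everyone occupying a rehabilitation bed on the census date. For a CCG's patients in that cohort, the chance of being in the independent sector is close to share = independent beds / all rehabilitation beds commissioned. The CCG figures below are assumptions for illustration; the article gives no CCG-level values.

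**Reading A: share / (population / 100,000).**

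- 50% share, population 200,000: 0.5 / 2 = 0.25
- 50% share, population 1,000,000: 0.5 / 10 = 0.05
- 50% share at 150,000, 300,000 and 600,000: 0.5 / 1.5 = 0.33, 0.5 / 3 = 0.17 and 0.5 / 6 = 0.08
- 25% share at 300,000: 0.25 / 3 = 0.08, the same score as a 50% share at 600,000

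With identical outsourcing, the spread in the score is simply the population ratio: fivefold in the first pair, fourfold in the trio.

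**Reading B: independent beds / (population / 100,000).**

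- 10 independent and 10 NHS beds per 100,000: score 10, share 10/20 = 50%
- 10 independent and 2 NHS beds per 100,000: score 10, share 10/12 = 83%
- Population 300,000, 9 of 12 beds independent: 9 / 3 = 3.0, share 75%
- Population 300,000, 9 of 36 beds independent: 9 / 3 = 3.0, share 25%
- Population 300,000, 50% share: 6 / 3 = 2.0 with 12 beds in total, 24 / 3 = 8.0 with 48

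**How much outsourcing information remains.** A simulation used assumed inputs: 191 CCGs, share drawn from Beta(2,2), median population 250,000 with log-SD 0.3 to 0.7, median supply 8 beds per 100,000 with log-SD 0.2 to 0.6, all independent. Mean correlations were:

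| Reading | With the true share | With the contaminant |
|---|---|---|
| A, share / population | 0.80 down to 0.46 | population, about −0.5 to −0.6 |
| B, beds per head | 0.90 down to 0.53 | total beds per head, 0.40 to 0.78 |

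The squared correlations with the share run from 0.64 down to 0.21 under A and from 0.80 down to 0.28 under B. These are unweighted CCG-level values. They show direction and rough size, not the strength that the real first stage would have.

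**Does a bed share remove length of stay?** Not fully. The Background reports independent-sector admissions twice as long as NHS ones. A CCG that sends half its admissions to each sector would then have a bed share of (0.5 × 2) / (0.5 × 2 + 0.5 × 1) = 67%, not 50%.

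**The case against.** The best defence is that this is a slip of wording. The concept, the sample size section, the sensitivity wording and the word proportion itself all fit a share; only the population tail does not. A condensed article may also leave the exact construction of a variable to a fuller document. The intention may well be a share, but the article does not leave the construction open. It states a definition, and an analyst who follows it gets a different variable.

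Three stronger readings are tempting, and the documents do not support them.

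- **That the variable no longer measures outsourcing.** Under both readings it still rises with the share, and under B it is a per-head volume of outsourcing.
- **That the Component 4 estimate will be biased, or that the exclusion condition is broken.** The article gives no relation between CCG size or bed supply and an individual's bed days other than through sector. The risk is plausible but not shown. Part of it is CCG-level confounding, which threatens independence rather than exclusion.
- **That a bed share cures everything, provided total beds per head is also adjusted for.** The 67% example shows that a bed share still reflects length of stay. Total bed supply may itself be a consequence of outsourcing if outsourcing lengthens stays, so adjusting for it could introduce bias.

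The planned balance check and adjusted sensitivity analysis are a partial safeguard, and their list of factors is only illustrative. They do not repair the definition or alter the main model.

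**Conclusion.** The definition is incoherent as printed and inconsistent with the other two descriptions of the instrument in Component 4. Followed literally, it gives different scores to CCGs with the same outsourcing (0.25 against 0.05 in the assumed example) or the same score to CCGs with different outsourcing (50% and 83%, both 10 per 100,000). It is a weaker predictor of sector than the share and may be related to bed days through CCG size or bed supply, neither of which the main model includes. The flat statement that the IV conditions are met is therefore not supported for the variable as defined.

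The size of any effect on the Component 4 result cannot be derived from the article. The numerical examples and the simulation rest on assumed CCG populations and bed counts. The sample size figures of 623 and 3,740 stand.

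**What to change.** Delete the population denominator and define the instrument once: the CCG's independent-sector rehabilitation beds divided by all rehabilitation beds it commissions, ranging from 0 to 1 and measured before the census date of 1 February 2021. Use that definition in the Component 4 opening text, sample size section and analysis section, and build the sensitivity thresholds on it. State as a limitation that a bed share still partly reflects length of stay.

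If a per-head rate is really intended, say so and justify the IV conditions for that variable, including why bed supply should be related to bed days only through sector. Adjustment for total beds per 100,000 belongs at most in a sensitivity analysis, because bed supply may itself be affected by outsourcing.

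The cost is one sentence and consistent wording in three places. The article says that the CQC has already shared the data for building the variable for every CCG. This assumes that those data hold total as well as independent-sector beds and predate the census, which should be confirmed. No new data collection or sample size revision follows.
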